### Procedure for unblinding if needed {17b}

Not applicable

## Data collection and management

### Plans for assessment and collection of outcomes {18a}

The primary outcome, i.e. number of hospital days within the last year prior to the end and the beginning of the intervention, will be sourced from the registers of the collaborating health insurance companies. The information provided in these registers can be assumed to be reliable and valid. The secondary outcomes will be collected using questionnaires sent via postal letter. Most of the secondary outcomes will be assessed using questionnaire modules that are widely accepted in science and for which empirical evidence for their reliability and validity exists. This is the case for self-efficacy with regard to health-related self-management [34, 35], for loneliness [36, 37], for depression [38], for anxiety [38], and for self-reported physical health, which will be determined using the four physical items of the EQ-5D-5L [30]. Self-reported physical activity will be assessed using a modified version of the GLTEQ. The original form of the GLTEQ has been validated [31] and the validity of the modification of the GLTEQ (see Additional File 4) will be investigated in the context of the study. Nutritional behaviour will be assessed using a list of items of behaviour compiled by those responsible for the part of the PSG-leader course that addresses nutrition. The items referring to behavioural intention and perceived behavioural control for both physical activity and nutrition have been formulated according to principles established in social psychology.

### Plans to promote participant retention and complete follow-up {18b}

Regarding collection of data for the primary outcome (i.e. number of hospital days), no measures for promoting participant retention and completing follow-up will be required for the participants ensured at AOK RH or BARMER, because collection of these data will not depend on the cooperation of these. Participants ensured at other ensurance companies will be requested to ask their ensurance companies for the required information and to send this to the project team. Participants who do not react to the first request will get a second request 2 weeks later. Those who do not react to the second request will receive a third request. For the questionnaires an analogous procedure will be applied. For members of the intervention group, attendance at each PSG-meeting, collaboration in the telephone-based health coaching and use of the browser-based web portal will be documented.

### Data management {19}

All questionnaire data will be entered twice by two different persons. Using a software tool, a third person will then check agreement between the two data sets that result from this double entry. In those cases where the entries deviate, the third person will determine the correct entry by looking into the questionnaire. In those cases where the questionnaire answers are ambiguous, two persons will reach a decision via discussion as to what should be entered. Except for the modified GLTEQ, no range checks will be necessary for any further outcome. For the GLTEQ, values that are impossible to achieve in reality will be set as missing.

### Confidentiality {27}

Confidentiality will be ensured by the collaboration of three discrete organisational units that are all located at the IGKE Cologne. These units will be (1) the Trust Centre, (2) the Data Warehouse and (3) the Multiple Pseudonym Assignment Unit (MPAU). The Trust Centre will hold the data file in which the address data are combined with identification numbers. These numbers will be referred to as personal identification numbers. The Data Warehouse will hold data files in which the data collected during the evaluation are combined with a different kind of identification number. These identification numbers will be referred to as study identification numbers. The MPAU will generate and hold the list in which the personal identification numbers are assigned to the study identification numbers. All three organisational units are isolated from each other both digitally and in terms of personnel.

To obtain the register data from the collaborating health insurance companies (i.e. AOK RH and BARMER), the Trust Centre will send the data file containing the address data and the personal identification numbers to these companies. In addition, the MPAU will send them the list with the assignment of the personal identification number to the study identification number. AOK RH and BARMER will identify the records belonging to the address data, assign them to the study identification numbers and send the records with the study identification numbers to the Data Warehouse. The Data Warehouse, in turn, will send these data to the organisational units responsible for analysing the data.

To obtain the survey data, the Trust Centre will prepare the envelopes that contain the questionnaires with the personal identification numbers on the envelope and deliver these envelopes unsealed to the MPAU. The MPAU will paste the study identification numbers that correspond to the respective personal identification numbers onto the questionnaires, put the questionnaires back into their envelopes, seal the envelopes and deliver the sealed envelopes to the Trust Centre. The Trust Centre will then paste the addresses belonging to the personal identification numbers over the personal identification numbers on the envelopes and sends these envelopes to the study participants. The completed questionnaires with the study identification number will be returned to TRAc Bamberg, which will be responsible for data entry. TRAc Bamberg will deliver the files of questionnaire data with the study identification numbers to the Data Warehouse and solely the study identification numbers of the returned questionnaires to the MPAU. The MPAU will identify the corresponding personal identification numbers and transmit these numbers to the Trust Centre. The Data Warehouse will then transfer the questionnaire data with the study identification numbers to the organisational units responsible for analysing the data.

None of the members of the MPAU will have access to the data held by the Trust Centre or the Data Warehouse and vice versa. As a result, no staff member of these units will be able to assign the address data to the questionnaire data or to the records of the statutory health insurance companies. Moreover, none of the people analysing the data will have access to the list in which the address data are assigned to personal identification numbers. They will therefore not be able to assign the data to specific participants.

The data flow for health literacy and patient activation will be handled differently, because these data will be used to decide whether the participants are to receive telephone-based health coaching or not. The values for both variables will be transmitted, together with participants’ study identification numbers, to the MPAU. The MPAU will replace the study identification numbers with the corresponding personal identification numbers and transmit the resulting file to the Trust Centre. The Trust Centre will then replace the personal identification numbers with the identifying personal information and transmit the resulting data to those responsible for contacting study participants to offer them the telephone-based health coaching service. The participants will be informed in the survey that these data will be treated in this way.

### Plans for collection, laboratory evaluation and storage of biological specimens for genetic or molecular analysis in this trial/future use {33}

Biological specimens will not be collected in this study.

## Statistical methods

### Statistical methods for primary and secondary outcomes {20a}

To test the effect of the intervention on the primary outcome (i.e. on number of hospital days), the number of hospital days directly before the start of the intervention and the number of hospital days directly before the end of the intervention will be determined. The differences between these numbers will be computed, and the intervention and control groups will be compared with regard to these differences using a *t*-test for independent samples.

As outlined above (see the ‘Objectives {7}’ section), the effect of the intervention on the number of hospital days is assumed to be mediated by several different variables. Each step of the mediation will take some time. For this reason, there may well be no effect on the primary outcome although effects on the preceding variables are already identifiable. Such a pattern of results would also indicate an effect of the intervention. Consequently, if there is no statistically significant effect for the primary outcome, the pattern for the secondary outcomes will be applied in order to decide the effectiveness of the intervention. For this purpose, all secondary variables will be z-transformed and poled so that higher numbers mean better outcomes in all variables. All variables transformed in this way will be subjected to a two-factorial analysis of variance with the variables as a within-subjects factor and the study condition as a between-subjects factor. The intervention will be judged as effective if there is a statistically significant effect in favour of the intervention group. To judge whether the secondary outcomes actually determine the primary outcome, the relationships between secondary outcomes and primary outcome will be analysed using a cross-lagged panel approach with data from baseline and end surveys as predictors and the number of hospital days for the corresponding time intervals as criteria.

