#### 12.2 Analysis metric

The analysis metric consists in changes from baseline.

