### Sample size {14}

The most important analysis in the evaluation addresses the effect of the intervention on the primary outcome, i.e. the number of hospital days. As mentioned above, intervention and waiting control group will be compared with regard to the change scores of hospital days. These change scores will be computed by subtracting numbers of hospital stays 1 year before intervention start from numbers of hospital stays 1 year before the intervention end. The comparison of change scores will be performed using a *t*-test for independent samples. The sample size has been determined with regard to this test. The basic demand was that the test should be able to detect an effect of size 0.2 with a significance level of 0.05 and a power of 0.8. An effect size of 0.2 is a small effect according to Cohen [39]. However, unpublished analyses of our own with numbers of hospital days indicate that the standard deviation of change scores of hospital days will be between 5 and 10. In this case, an effect size of 0.2 would correspond to differences of one to two hospital days. Even a difference of only one day would mean a substantial difference in costs.

Further conditions presupposed for determining the sample are:
Two percent of the included persons could die during the intervention period or withdraw their consent for their data to be used.There could be a dropout rate of 15% in the intervention group and 20% in the waiting control group. The reason for this assumption is that up to 50% of the sample might consist of persons who are not ensured at AOK RH or BARMER. For these persons, the numbers of hospital days will not be provided directly by the health insurance companies. Instead, the patients will have to request the data from their health insurance companies and then transfer them to the project team. Several patients will not do this, with patients in the waiting control group being more likely not to do this. Within this sub-sample, a dropout rate of 30% in the intervention group and 40% in the waiting control group seems realistic. This would correspond to dropout rates of 15% and 20% in the total sample.The allocation ratio of intervention to control is 6:7.The sample size should be divisible by 13 because of the allocation ratio.

All these considerations imply a sample size of 1001.

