## Assignment of interventions: allocation

### Sequence generation {16a}

The randomisation will be stratified with regard to the six areas for which the participants have been recruited and with regard to the status of the participants, i.e. PSG leader versus common PSG member. Accordingly, there will be 12 different strata combinations. For each of these combinations, a specific allocation sequence will be applied. The first author of the protocol, who is also the chief evaluator of the project, will generate these sequences. The sequences will contain blocks to ensure that the actual distribution of intervention and waiting control patients in each strata combination is always close to the envisaged ratio of 6 to 7. Moreover, to ensure that assignments to the two study conditions cannot be predicted based on the preceding assignments, the assignments will be performed weekly and those parts of the allocation sequences applied for the respective week will be always brought into a new random order.

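### The primary t-test on change in hospital days fixes the baseline slope at 1 and omits the randomisation strata, giving up precision by an amount that depends on an unreported correlation

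*Protocol article*

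**What the plan says.** The analysis is fixed in several places in the protocol article.

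- Section 12.2 sets the metric for all outcomes: "The analysis metric consists in changes from baseline".
- Section 12.4 defines the primary change score as hospital days in the year ending at month 18 minus hospital days in the year before the intervention starts.
- Section {20a} says of the hospital days before the start and before the end: "The differences between these numbers will be computed, and the intervention and control groups will be compared with regard to these differences", by a two-sample t-test. It names no covariate.
- Section {14} sizes the trial on the same test, which should "detect an effect of size 0.2 with a significance level of 0.05 and a power of 0.8". The planning figure is that "the standard deviation of change scores of hospital days will be between 5 and 10".
- Section {16a} states: "The randomisation will be stratified with regard to the six areas for which the participants have been recruited". PSG leader versus ordinary member is the second factor, which gives 12 strata.

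The only regression models named for treatment comparisons are the subgroup interaction models in section {20b}, and no baseline or stratum adjustment is stated for them. No correlation between the two years' hospital days appears anywhere.

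Section {14} also describes the change score as "subtracting numbers of hospital stays 1 year before intervention start from numbers of hospital stays 1 year before the intervention end". The outcome, the standard deviation and the effect in that same section are all in days.

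**The concern.** A change score uses the baseline value, but with a coefficient fixed in advance at 1. Regression on baseline estimates that coefficient. If the true slope is well below 1, subtraction adds the noise of the baseline year to the outcome. With equal variances and a correlation below 0.5, the change score is more variable than the follow-up value alone.

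Every patient in the planned test must already have a baseline value, and area and leader status are known for everyone randomised. Using this information costs no data. The Discussion says that the target of 1001 may not be reached because the pandemic hindered recruitment. A trial that may fall short has most reason not to give up precision on its primary outcome.

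**Working it through.** **Inputs from section {14}.** Standardised effect 0.2 on the change-score SD; significance level 0.05; power 0.8; allocation 6:7; 2% death or withdrawal of consent; dropout 15% (intervention) and 20% (control); N a multiple of 13; SD of change 5 to 10 days. Sidedness is not stated. Two-sided is assumed, because a one-sided test would need only 780.

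**Step 1: reproduce the plan's figure.** Of 1001 patients, 462 and 539 are allocated. Evaluable numbers are:

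- intervention: 462 × 0.98 × 0.85 = 384.8
- control: 539 × 0.98 × 0.80 = 422.6

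The noncentral t gives power 0.809 for an effect of 0.2. The smallest multiple of 13 that reaches 0.80 is 988, which is 1.3% below 1001. The stated size reproduces.

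**Step 2: compare the variances.** Let s0 and s1 be the SDs of hospital days in the baseline and follow-up years, and rho their correlation within arm.

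- Change score: s0² + s1² − 2·rho·s0·s1
- Baseline-adjusted residual: s1²(1 − rho²)
- Difference: (s0 − rho·s1)², which is never negative and is zero only when the true slope on baseline is 1

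In large samples under this common-slope model, adjustment is therefore never less precise. With s0 = s1 = s, the two variances are 2s²(1 − rho) and s²(1 − rho²), so their ratio is (1 + rho)/2. Relative to the follow-up value alone, the change score has 2(1 − rho) times the variance: 1.8 at rho 0.1, 1.4 at 0.3 and 1.0 at 0.5.

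**Step 3: put the numbers in.** The same absolute difference is tested on the same 385 + 423 patients, so the effect becomes 0.2/√((1 + rho)/2). The half-width of the 95% interval is 1.96 × SD × √(1/384.8 + 1/422.6) for the t-test, multiplied by √((1 + rho)/2) after adjustment. Rho is an assumption, so the range is shown.

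| Analysis | Fall in SE | Power at 1001 | N needed | 95% CI half-width, days (change SD 5 to 10) |
|---|---|---|---|---|
| Change-score t-test | – | 0.809 | 988 | 0.69 to 1.38 |
| Adjusted, rho 0.1 | 26% | 0.969 | 546 | 0.51 to 1.02 |
| Adjusted, rho 0.3 | 19% | 0.940 | 637 | 0.56 to 1.11 |
| Adjusted, rho 0.5 | 13% | 0.906 | 741 | 0.60 to 1.20 |
| Adjusted, rho 0.7 | 8% | 0.868 | 832 | 0.64 to 1.27 |
| Adjusted, rho 0.9 | 3% | 0.829 | 936 | 0.67 to 1.35 |

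**Step 4: check with skewed data.** An illustrative simulation used assumed parameters: zero-heavy, skewed days, change SD about 8, 600 trials per setting, no stratum effects. With no treatment effect, the variance ratio was 0.71, 0.58 and 0.49 at correlations of 0.39, 0.16 and 0.06. The formula gives 0.69, 0.58 and 0.53. Type I error was 0.04 to 0.06 for the t-test and 0.03 to 0.06 for regression with robust standard errors. With a 40% reduction in the rate of stays, power was 0.45 to 0.47 for the t-test and 0.67 to 0.78 for regression.

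**Step 5: strata.** The gain from area and leader status equals the share of residual outcome variance that they explain. The protocol gives nothing from which to compute it.

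**The case against.** The strongest reply is that nothing here is wrong in the sense of invalid. Under randomisation the change-score t-test is unbiased, the trial was sized for exactly this test, and the size reproduces. The benefit of adjustment rests on a correlation that the protocol does not report. At 0.7 or above, the standard error falls by 8% or less. All of that stands, and it limits the point to efficiency.

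Several stronger readings are tempting, and the document does not support them.

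- *The test ignores baseline.* It does not. Sections 12.4 and {20a} subtract it for every patient. Only the slope is fixed, and only the strata are unused.
- *Adjusted estimates would be far tighter.* That holds at low correlations only. A weak correlation between two years' hospital days is plausible, but it is an assumption.
- *Leaving out the strata makes the reported error wrong.* It tends to make the standard error somewhat too wide, and only if area or leader status predicts hospital days. The direction is conservative, so false positives are not inflated.
- *The same change should be carried to the questionnaire outcomes.* Section {20a} puts these, z-transformed, into one two-factor analysis of variance. Adjustment within that model would need its own specification, and no correlations are given for those variables.
- *The primary outcome is ambiguous between stays and days.* The same section {14} speaks of change scores of hospital days, and section 12.4 defines the subtraction in days. It is a wording slip and adds no weight to the point on adjustment.

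**Conclusion.** The point holds as a loss of precision, not as an error of validity. Its direction does not depend on the correlation, because under the model in step 2 the adjusted analysis is at least as precise whatever the correlation. Its size does: the reduction in standard error runs from about 26% at a correlation of 0.1 to about 3% at 0.9, and power at the planned size rises from 0.81 to between 0.97 and 0.83. These figures assume equal variances in the two years, a two-sided test and the protocol's own attrition rates. The further gain from the strata cannot be quantified. The change is worth making because the information is already held and the recruitment target is in doubt. It ranks below defects that would bias the result or inflate the error rate.

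**What to change.** Make the primary analysis a linear regression of hospital days in the year before month 18 on study condition, adjusted for hospital days in the year before the start, area (six levels) and PSG-leader status, with heteroscedasticity-robust standard errors. Report the adjusted mean difference in days with its 95% confidence interval. Keep the change-score t-test as a sensitivity analysis. Retain 1001 as a conservative sample size.

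As a separate editorial correction, replace hospital stays by hospital days in the description of the change score in section {14}.

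No extra data or patients are needed. The cost is a routine amendment under section {25}: agreement with partners and sponsor, submission to the ethics committee and a registry update. Recruitment began in December 2020, and section {17a} says that the analysts are not blinded. The amendment should therefore be dated before any hospital-day data arrive. Section 12.4 allows this, since the collaborating insurers supply those data only after the intervention.

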## Objectives {7}

### Primary hypothesis

P-SUP reduces the number of hospital days.

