#### 12.5 Explanations

The number of hospital days has been chosen as the primary outcome because hospital days constitute a major cost factor in the treatment of T2DM and CHD. A special outcome measure referring to possible physical harms of the intervention will not be applied because of the negligible probability of physical harms being caused by the intervention. However, each of the selected outcome measures can be used to detect negative effects of the intervention.

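### The fallback verdict is conditioned only on a non-significant hospital-day test, so P-SUP can be judged effective while the hospital-day estimate points to an increase

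*Protocol article*

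**What the plan says.** The primary hypothesis is directional: "P-SUP reduces the number of hospital days". Under Statistical methods for primary and secondary outcomes {20a}, change scores in hospital days are compared by an independent-samples t-test. The article then argues that, because each mediation step takes time, "there may well be no effect on the primary outcome although effects on the preceding variables are already identifiable". From this it derives a rule: "if there is no statistically significant effect for the primary outcome, the pattern for the secondary outcomes will be applied in order to decide the" question of effectiveness. The secondary variables are z-transformed, aligned so that higher is better, and analysed jointly in a two-factor analysis of variance. The criterion is: "The intervention will be judged as effective if there is a statistically significant effect in favour of the intervention group".

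Two other places bear on the point. Section 12.5 Explanations declines a separate measure of physical harm and adds that "each of the selected outcome measures can be used to detect negative effects of the intervention". Sample size {14} expects that "the standard deviation of change scores of hospital days will be between 5 and 10" and remarks: "Even a difference of only one day would mean a substantial difference in costs".

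**The concern.** This is a complete decision rule, not a detail left for an analysis plan, and its rationale is narrower than its trigger. Delayed mediation explains a flat or mildly favourable hospital-day result. It does not explain an estimate showing more hospital days in the intervention arm. The rule treats both alike, because a non-significant test is read as no effect yet.

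Nothing else in the article closes the gap. The cross-lagged analysis in the same section does not feed into the verdict, and the statement in 12.5 that the outcomes can reveal negative effects has no decision attached. The verdict matters because the abstract says that an effective intervention may be included in the disease management programmes. It could be reached from unblinded self-reports while the primary outcome points against the primary hypothesis.

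**Working it through.** **Inputs (Sample size {14}).** Total 1001; allocation 6:7, so 462 intervention and 539 control; 2% death or withdrawal of data; dropout 15% and 20%; effect size 0.2; alpha 0.05; power 0.80; SD of change scores 5 to 10 days. The article does not state whether the test is one- or two-sided.

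**Reproducing the plan's figure.** I took the smallest total divisible by 13 that reaches 80% power at effect size 0.2 after these losses.
- Two-sided 5%: 988 (power 0.804), within 1.3% of 1001. At 1001 the power is 0.809.
- One-sided 5%: 780, which does not match.

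The plan is therefore consistent with two-sided testing, which I use below.

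**Evaluable numbers.** 462 × 0.98 × 0.85 = 385; 539 × 0.98 × 0.80 = 423.

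**Non-significant zone.** The standard error of the difference is SD × √(1/385 + 1/423) = SD × 0.0704. With critical t = 1.963, the largest non-significant observed difference is SD × 0.138.

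**Chance that a true 1-day rise is non-significant.** This is one minus the noncentral-t power at effect size 1/SD.

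| SD | Standard error (days) | Largest non-significant observed rise (days) | True 1-day rise non-significant | of which estimate below zero |
|---|---|---|---|---|
| 5 | 0.352 | 0.69 | 19% | under 1 point |
| 7.5 | 0.528 | 1.04 | 53% | about 3 points |
| 10 | 0.704 | 1.38 | 71% | about 8 points |

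The last column is approximately Φ(−1/standard error): Φ(−2.84), Φ(−1.89) and Φ(−1.42). Subtracting it, a true 1-day rise gives a non-significant estimate that points to an increase in about 19%, 50% and 63% of trials.

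**Observed 1-day rise.** It is non-significant once the SD exceeds 1/0.138, about 7.2. At SD 5, p = 0.005. At SD 7.5, p = 0.059. At SD 10, p = 0.16 with a 95% interval of −0.38 to 2.38 days.

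**Smaller trial.** The Discussion concedes that 1001 may not be reached. With assumed totals of 800, 600 and 500 and the same loss rates, the 7.2 threshold falls to 6.5, 5.6 and 5.1.

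**From open fallback to a verdict of effective (illustrative only).** The article gives no effect size for the composite. Suppose it improves by 0.2 SD, is independent of hospital days and has the same evaluable numbers (power 0.809). With a true 1-day rise, the rule then declares effectiveness in 0.191 × 0.809 = 15%, 0.528 × 0.809 = 43% and 0.706 × 0.809 = 57% of trials.

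**The case against.** The strongest reply is that the rule is not blind to harm. A significant increase is itself a significant effect on the primary outcome, so read literally it does not open the fallback. A true 2-day rise would be missed in about 0.01%, 3% and 19% of trials at SD 5, 7.5 and 10. This stands, and it bounds the problem to differences of roughly 0.1 to 0.2 SD.

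Several stronger readings are tempting, and the article does not support them:
- *An observed 1-day rise would pass anywhere in the planned SD range.* At planned size it passes only above an SD of about 7.2.
- *A rise of any size would pass.* That needs a one-sided primary test, which does not reproduce 1001.
- *Hospital days are the sole harm signal.* Section 12.5 refers to every selected outcome. A data monitoring committee follows safety, and abnormalities are minuted in group meetings and coaching calls.
- *The exercise component could itself raise hospital days in coronary patients.* Nothing in the article supports this. It describes physical activity as favourable, excludes severe comorbidities and tailors exercises to the participants.
- *One day is a declared harm margin.* The remark concerns costs and was made about a benefit. Section 12.5 gives cost as the reason for choosing this outcome, so using one day as a yardstick for a rise is fair, but it remains a borrowed yardstick.

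A further objection is that confidence-interval reporting belongs in an analysis plan. That is true of the reporting itself, but the article fixes the verdict rule, and the rule does not use the interval. Nor is this only the multiplicity question. Splitting alpha would leave the gap, and a stricter primary alpha would make a rise more likely to be non-significant.

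**Conclusion.** The point holds in bounded form. The effectiveness verdict passes to self-reported outcomes after any non-significant hospital-day result, whatever its sign or upper confidence limit, although the rationale covers only an effect that has not yet appeared. A true 1-day rise would leave the fallback open in about 19%, 53% or 71% of trials at SD 5, 7.5 or 10. Observed rises stay non-significant up to 0.69, 1.04 or 1.38 days.

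These figures assume two-sided testing at 5%, the planned losses and an approximately normal test statistic. How often a verdict of effective would follow depends on a composite effect and a correlation that the article does not give, so the 15%, 43% and 57% should not be quoted as properties of the trial. The theoretical frame treats the secondary outcomes as mediators of hospital days, so independence is a simplification.

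**What to change.** In Statistical methods {20a}, replace the fallback verdict with wording such as:

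> If the primary test is not significant, a significant composite result in favour of the intervention supports a conclusion of an effect on self-reported intermediate outcomes only. The difference in hospital days is reported with its 95% confidence interval. If the upper limit exceeds +1 day, the conclusion states that a relevant increase in hospital days is not excluded.

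In 12.5 Explanations, add that absence of a negative effect on hospital days is judged from this interval and not from p > 0.05.

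The change takes a few sentences and needs no new data or participants. The cost is that an unqualified claim of effectiveness becomes harder to reach. With no true difference, the upper limit falls below +1 day in about 81%, 47% or 29% of trials at SD 5, 7.5 or 10, so the caveat would be attached in the remaining 19%, 53% or 71%. A further condition, that the estimate must not favour control, is optional. It would block half of the trials with no true difference, which is the situation the fallback was written for.
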